## Abstract

**Background:**

Knee osteoarthritis (OA) causes substantial pain, physical dysfunction and impaired quality of life. There is no cure for knee OA, and for some people, the disease may involve progressive symptomatic and structural deterioration over time. Platelet-rich plasma (PRP) is a therapeutic agent that aims to address underlying biological processes responsible for OA pathogenesis. As such, it has the potential to improve both symptoms and joint structure. The aim of this clinical trial is to determine whether a series of injections of PRP into the knee joint will lead to a significantly greater reduction in knee pain, and less loss of medial tibial cartilage volume over 12 months when compared to a series of placebo saline injections in people with knee OA.

**Methods:**

This will be a two-group, superiority, randomised, participant-, interventionist- and assessor-blinded, placebo-controlled trial. Two hundred and eighty-eight participants aged over 50 years with painful knee OA and mild to moderate structural change on x-ray (Kellgren and Lawrence grade 2 and 3) will be randomly allocated to receive either three PRP injections or three normal saline injections into the knee joint at weekly intervals. The primary outcomes will be 12-month change in average overall knee pain severity (numeric rating scale) and medial tibial cartilage volume (magnetic resonance imaging (MRI)). Secondary outcomes include additional measures of knee pain and other symptoms, function in daily living and sport and recreation, quality of life, participant-perceived global ratings of change, and other MRI structural outcomes including meniscal and cartilage morphology, synovitis, effusion, bone marrow lesions and cartilage defects. A range of additional measures will be recorded, and a separate health economic evaluation will be performed.

**Discussion:**

The findings from this study will help determine whether PRP improves both clinical and structural knee OA outcomes over 12 months when compared to a series of placebo saline injections.

**Trial registration:**

Australian New Zealand Clinical Trials Registry reference: ACTRN12617000853347. Prospectively registered 9th of June 2017.

**Electronic supplementary material:**

The online version of this article (10.1186/s12891-018-2205-5) contains supplementary material, which is available to authorized users.

## Background

Osteoarthritis (OA) is a leading causes of global disability, and the number of people affected is anticipated to substantially increase over the coming decades [1]. Osteoarthritis at the knee joint, the most commonly involved lower limb site, can cause pain and physical dysfunction and impaired quality of life. There is no cure for knee OA, and to date, most research has focused on treatments to alleviate pain and prevent functional decline.

Recommended drug therapies (such as analgesics and anti-inflammatory agents) and non-drug therapies (such as exercise) have short-term clinical benefits, but effect sizes are small to moderate at best [2, 3]. Furthermore, drug therapies can have adverse events, while uptake and maintenance of exercise are often poor leading to lack of long-term benefit. Intra-articular therapies in clinical use for knee OA include glucocorticoids and hyaluronic acid (a viscosupplement). Intra-articular glucocorticoids are generally recommended [4–6], although not universally [7], and for short-term pain relief only given that benefits are limited to a few weeks [6, 8]. Furthermore, a recent clinical trial highlighted a potential small deleterious effect of repeated corticosteroid injections on knee joint cartilage [9]. Hyaluronic acid is controversial with most clinical guidelines advising against its use [4, 10], or providing an uncertain recommendation [6]. As knee OA is a chronic disease, with both symptoms and structural deterioration drivers for surgical joint replacement, identifying efficacious, safe treatments that address both is an important objective.

One therapy with the potential to address underlying biological processes responsible for OA pathogenesis is platelet-rich plasma (PRP), an autologous blood product that contains an elevated concentration of platelets. Activation of PRP releases an initial burst then a sustained release of growth factors and other molecules, including platelet-derived growth factor, transforming growth factor-β, type I insulin-like growth factor and vascular endothelial growth factor [11]. Animal studies have shown that these proteins are responsible for a range of critical tissue healing roles such as chondrocyte apoptosis inhibition, bone and vessel remodelling, inflammatory modulation, and importantly, collagen synthesis. Additionally, other bioactive molecules released by platelets, such as fibrin, act as a scaffold and chemo-attractant for further migration of stem and other cells to the damaged tissue [11]. Given the limited repair capacity of articular cartilage, these roles offer a mechanism by which PRP may enhance tissue healing and cartilage regeneration in knee OA.

There is some randomised controlled trial (RCT) evidence about the symptomatic effects of PRP for knee OA. A recent systematic review that included 14 RCTs concluded that PRP was likely to be more effective for pain relief and physical function when compared with control injections that included normal saline, HA or glucocorticoids [12]. However, all RCTs were found to be at a moderate to high risk of bias, and most lacked longer-term follow-up and were inadequately powered with small sample sizes. Only three trials compared PRP to placebo, with results showing significantly greater improvements in symptoms over normal saline at six [13] and 12 months [14, 15]. However, all three studies suffered from major methodological flaws including a lack of adequate blinding suggesting the benefits may have been overestimated. No study has investigated the structural effects of PRP.

Heterogeneity in the preparation and injection methods used by published studies has also limited the ability to determine optimal PRP protocols. However, protocol characteristics of those RCTs that have reported positive effects on pain and function have generally utilised a single centrifugation at a slower speed (approximately 1500 g) for approximately 5 min to yield leucocyte poor PRP, and injected fresh PRP (i.e. not frozen and then thawed for subsequent injections) over 3 injections at weekly intervals [16]. There is some preliminary evidence to suggest younger patients, and those with less severe radiographic disease may experience greater symptomatic benefits [14, 17–19].

The primary aim of this two-arm randomised, placebo-controlled trial is to determine if a series of injections of PRP into the knee joint leads to significantly greater reductions in average knee pain severity and less loss of medial tibial cartilage volume when compared to placebo saline injections over 12 months in people with symptomatic knee OA. The secondary aim is to determine if PRP has significantly greater benefits for other clinical (other knee pain measures, physical function, quality of life, participant global rating of change) and magnetic resonance imaging (MRI) structural outcomes (effusion, synovitis, cartilage morphology, bone marrow lesions, cartilage defects, meniscal morphology) compared to placebo injections at 2 (clinical) and 12 (clinical and MRI) months. We will also conduct an embedded economic evaluation of PRP if benefits are found.

## Methods/design

### Trial design

This protocol is described using the 2013 SPIRIT guidelines on standard protocol items for clinical trials [20]. The trial is designed as a two-group, superiority, randomised, participant-, interventionist- and assessor-blinded placebo-controlled trial, to be conducted in Melbourne and Sydney over 4 years. The primary end-point for analysis of outcomes is 12 months after baseline assessment.

### Participants

We will recruit 288 participants aged over 50 years with painful knee OA in one or both knees, and mild to moderately severe structural change on x-rays, from the community via advertisements, print/radio/social media, clinicians and our volunteer database. Participants are eligible for the study if they meet all inclusion criteria below:i.Aged > 50 years;ii.knee pain on most days in the last month;iii.have Kellgren and Lawrence grade 2 or 3 tibiofemoral OA on x-ray; andiv.report an average level of overall knee pain over the past week of at least 4 on an 11-point numeric rating scale in the target knee.

Participants will be excluded if they:i.have Kellgren and Lawrence grade 1 (indicating questionable disease) or grade 4 (indicating severe disease);ii.have lateral joint space narrowing greater than or equal to medial joint space narrowing on x-ray using the Osteoarthritis Research Society International (OARSI) atlas [21];iii.had injection into the target knee joint of glucocorticoid in the past 3 months or hyaluronic acid in the past 6 months,iv.had any autologous blood product or stem cell preparation in the past;v.had knee surgery on their target knee within past 12 months;vi.have systemic or inflammatory joint disease such as rheumatoid arthritis;vii.have a history of crystalline or neuropathic arthropathy;viii.had a knee joint replacement or high tibial osteotomy on their target knee;ix.plan for joint surgery in the target knee in next 12 months;x.have other muscular, joint or neurological condition affecting lower limb function;xi.have a needle phobia;xii.have immunosuppression or acute infective processes;xiii.have cancer or other tumours in the last 3 years, or undergone any treatment for cancer or tumours in the last 3 years;xiv.have a bleeding disorder or are receiving anti-coagulation therapy;xv.have the presence of a warm, tense joint effusion;xvi.have a platelet count < 150,000/μL;xvii.have any other medical condition precluding participation in the study including contraindication to MRI such as a pacemaker;xviii.pregnancy;xix.are unwilling to discontinue non-steroidal anti-inflammatory drug and other analgesic usage, with the exception of paracetamol for rescue pain relief, from 2 weeks before the baseline assessment until the 12-month follow-up assessment;xx.have a body mass index (BMI) > 40 kg/m^2^ because of problems fitting into the MRI machine knee coil;xxi.unable to attend the six study appointments over 12 months; andxxii.cannot understand written/spoken English.

### Procedures

Figure 1 and Table 1 outline the trial phases and the schedule for enrolment, screening, interventions and assessments. Participants will complete an online survey to determine initial eligibility and will then be screened over the telephone by one of the researchers. Participants deemed suitable from the telephone screening will be invited to undergo standardized bilateral posteroanterior radiographic and blood screening. Participants who pass telephone, radiographic and blood screening will be invited to attend an appointment with the local site coordinator at either the Department of Physiotherapy at the University of Melbourne in Victoria or the Royal North Shore Hospital in New South Wales, Australia. At this visit, the site coordinator will perform a physical assessment of the knee, and participants who do not have a warm, tense knee effusion will then be deemed suitable for the study. Eligible participants will then complete the baseline clinical and health outcome questionnaire, either on paper or electronically on a PC depending on their preference, and will then attend one of the radiology centres for their baseline knee MRI scans. For those participants with bilaterally eligible knees, the most symptomatic knee will be deemed the study knee. Participants will be asked to discontinue non-steroidal anti-inflammatory drugs and other analgesics for knee pain, with the exception of paracetamol for rescue pain relief, from 2 weeks before the baseline assessment until the 12-month follow-up assessment.

**Fig. 1 Fig1:**
[figure not shown]
Flow diagram of the study protocol

**Table 1 Tab1:** SPIRIT (Standard Protocol Items: Recommendations for Interventional Trials) diagram of enrolment, interventions and assessments for the RESTORE trial

Timepoint			Study period						
	Enrolment	Baseline	Injection 1	Injection 2	Injection 3	Post-allocation			Close-out
	-t_1_		0	1w	2w	2 m	6 m	9 m	12 m
Enrolment:									
Eligibility screen	X								
Informed consent	X								
Allocation		X							
Interventions:									
Platelet rich plasma			X	X	X				
Saline			X	X	X				
Assessments:									
Primary outcomes									
Average overall knee pain severity		X				X	X	X	X
Medial tibial cartilage volume		X							X
Secondary outcomes									
Walking pain severity		X				X			X
KOOS		X							
ICOAP		X							
Participant global ratings of change						X			X
AQoL-8D		X				X	X	X	X
MOAKS sub-scores		X							X
BML and cartilage defects score		X							X
Other measures									
Drug/supplement use		X				X			X
Cytokines and growth factors			X	X	X				
Number of injections			X	X	X				
Adverse events, co-interventions						X			X
Success of blinding					X				
Descriptive measures									
Weight, height, BMI		X							X
Age, gender, symptom duration, x-ray severity, knee alignment, employment, symptom laterality, other symptoms, treatment expectation, PainDETECT, PASE, knee effusion		X							
Health economic data									
QALYs, cost-effectiveness ratio, WHOHPQ		X				X	X	X	X

*ICOAP* Intermittent and Constant Osteoarthritis Pain, *KOOS* Knee Injury and Osteoarthritis Outcome Score, *AQOL-8D* Assessment of Quality of Life Instrument (8D version), *MOAKS* Magnetic resonance imaging OA Knee Score, *BMI* Body mass index, *PASE* Physical Activity Scale for the Elderly, *QALYs* Quality Adjusted Life Years, *WHO HPQ* World Health Organisation Health Performance Questionnaire

Paper-based or electronic clinical and health outcome questionnaires will be sent to participants at 2, 6, 9 and 12 months to complete primary and secondary outcomes at home. Structural outcome measures recorded using MRI of the knee joint will be conducted at baseline and 12 months at radiology practices in Melbourne and Sydney. Ethical approval has been obtained from the University of Melbourne Human Research Ethics Committee (HREC No. 1647671) and the Northern Sydney Local Health Districts Human Research Ethics Committee (HREC/16/HAWKE/430). All participants will provide written informed consent.

#### Randomisation procedures

Participants will be randomly allocated by telephone to the PRP injection group or the placebo injection group using a randomisation schedule prepared and stored by the National Health and Medical Research Council (NHMRC) Clinical Trial Centre. Randomisation will occur according to a 1:1 allocation ratio in blocks with varying sizes of 6 or 10, stratified according to site (Melbourne or Sydney) and radiographic disease severity (Kellgren and Lawrence grades 2 or 3). At the first treatment appointment, a study nurse will telephone the NHMRC Clinical Trials Centre just before administration of the first injection to reveal the participant’s group allocation.

#### Blinding arrangements

Participants will not be told until the end of the study which group they were allocated to. Blood will be withdrawn from the arm of participants in both groups to ensure participant blinding. Blood from participants in the placebo group will be disposed of by the study nurse in a separate location. A study nurse will prepare the injection in a separate room and place a patient label over the syringe and needle base to occlude the contents. The nurse will then give the syringe to the injecting doctor who will not know or be able to tell whether the syringe has PRP or saline. The same preparation process will be in place for injection appointment 2 and 3. All clinical and MRI assessments will be conducted by an assessor blinded to treatment allocation.

#### Interventions

Participants in both the PRP and placebo groups will undergo three intra-articular knee injections performed at weekly intervals, in line with commonly used injection protocols for this condition [16, 22]. The doctor will give the participant the option of having a local anaesthetic injection superficially (subcutaneously) before treatment. The doctor will then check the study knee for the presence of an effusion using ultrasound. If present and deemed to be amenable to aspiration, then this will be performed using a needle inserted in the suprapatellar bursa, and the volume aspirated will be recorded. The study nurse will give the doctor an occluded syringe with a needle containing 5 ml of either normal saline or PRP, and the contents will be injected into the knee joint under ultrasound guidance using a medial patellofemoral approach. Following the injection, passive knee flexion and extension will be performed five times with the participant observed resting for 10 min thereafter.

Participants will return for their second injection approximately 1 week later, and again for a third and final injection approximately 1 week after that. The injection process will be the same as the first injection. After the third injection, participants will be asked about which group they believe they are in, and separately the injecting doctors will also be asked which group they believe the participant is in. After each injection, the study nurse will ask the participant if they experienced any adverse events following the previous injection.

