#### PRP preparation

Platelet-rich plasma will be prepared using a commercially-available product (Regen Lab SA), which yields a platelet concentration factor of 1.6 to 5 times over whole blood values, and with approximately 80% platelet recovery [23]. After the blood draw into the Regen blood collection tubes, the tube will be gently inverted several times to mix the anti-coagulant with the blood sample. Samples will then be centrifuged at 1500 g for 5 min in a separate room by the study nurse. After centrifugation, the tubes will be gently agitated to ensure all visible platelet aggregates detach from the separating gel and the tube wall, and 5 mL will be gently withdrawn into a syringe. At the Melbourne site only, a portion of the PRP (approximately 4 mL) will be withdrawn and saved for analysis. A video of the PRP preparation procedure can be found in at https://www.youtube.com/watch?v=Cq8UlbL18Yg&feature=youtu.be.

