### Adverse effects of treatment and co-interventions

Adverse events are defined as any untoward medical occurrence in a trial participant which does not necessarily have a causal relationship with the treatment. Adverse events will be collected via self-report during the 2- and 12-month data collection, and by the study nurse following each injection. This will include questions about any adverse events that participants believe may be related to the study intervention, including their nature, how long they lasted for and what action if any, they took (e.g. taking medication or seeing a health professional). Serious adverse events are defined as any untoward and unexpected medical occurrence that results in death, is life-threatening, requires hospitalisation or prolongation of existing inpatient’s hospitalisation, results in persistent or significant disability or incapacity, is a congenital anomaly or birth defect, or any other important medical condition which may require medical or surgical intervention to prevent one of the outcomes listed [39]. Use of co-interventions (medications for knee pain and any other treatments for knee OA) will be recorded at 2 and 12-months.

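### Adverse events around the injections are elicited by the study-nurse role, which knows the allocation, although the article says all clinical assessments are blinded

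*Protocol article*

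**What the plan says.** Randomisation procedures states who learns the allocation: "a study nurse will telephone the NHMRC Clinical Trials Centre just before administration of the first injection to reveal the participant’s group allocation". According to Blinding arrangements, a nurse also makes up the syringe out of sight and hides what it holds behind a label, with the same routine for injections 2 and 3. That section adds: "Blood from participants in the placebo group will be disposed of by the study nurse in a separate location". Under PRP preparation: "Samples will then be centrifuged at 1500 g for 5 min in a separate room by the study nurse". The Interventions section has the study nurse hand the covered syringe to the doctor.

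The Interventions section also gives this role the safety enquiry: "After each injection, the study nurse will ask the participant if they experienced any adverse events following the previous injection". The section on adverse effects and co-interventions names two routes for adverse events: self-report at 2 and 12 months, and collection "by the study nurse following each injection".

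Blinding arrangements closes with: "All clinical and MRI assessments will be conducted by an assessor blinded to treatment allocation". No exception is stated. Adverse events are listed among the additional measures under Outcome measures. In Table 1 they stand in the Assessments block, marked at 2 and 12 months only.

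**The concern.** The role that must know the treatment in order to prepare it is also the role that asks about reactions to it. Complaints such as soreness or swelling after a joint injection are partly subjective. Whether they are recorded can depend on how the question is put, how far a vague answer is followed up, and whether the questioner counts it as an event. If any of these shifts with knowledge of the arm, the recorded frequencies can differ between arms when the true frequencies do not, or a true difference can be hidden.

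The article describes no other route for events in the injection period until the 2-month self-report. A reader relying on the blinding statement would take the injection-period safety data to be blinded, when by the article's own account they are not.

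**Working it through.** **Step 1: does the role that asks know the allocation?**

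| Task | Who | Section |
|---|---|---|
| Telephones for the allocation | a study nurse | Randomisation procedures |
| Prepares and covers the syringe | a study nurse | Blinding arrangements |
| Discards placebo-group blood | the study nurse | Blinding arrangements |
| Centrifuges the blood for PRP | the study nurse | PRP preparation |
| Hands the syringe to the doctor | the study nurse | Interventions |
| Asks about adverse events | the study nurse | Interventions; Adverse effects |

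The Interventions section uses one term for handing over the syringe and for asking about events. No second, blinded nurse is described. On the text, the answer is yes for the role. That one individual does both tasks is an inference from the role name.

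**Step 2: does this contradict the blinding statement?** That statement covers all clinical assessments without exception, and Table 1 files adverse events under Assessments. Read together, these cannot both stand beside the nurse's question. The Trial design section claims blinding of participant, interventionist and assessor. The nurse is not among them.

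**Step 3: do the time points agree?** Table 1 marks adverse events at 2 and 12 months and at no injection visit, while two sections of text place the nurse's question there. The two sections also differ. The Interventions wording looks back to the previous injection, so there is nothing to ask about at the first visit, and events after injection 3 wait for the 2-month self-report. The adverse-effects section speaks of collection following each injection, which would close that gap. The timing point applies equally to both arms and is not itself a blinding flaw.

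**Step 4: what could the size be?** The article states no adverse-event rate, so there is no figure to reproduce. The following is illustration only. Assume the same true proportion p with an event in both arms, detection s1 in one arm and s0 in the other, and the planned 144 per arm.

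- Recorded proportions: p × s1 and p × s0.
- Spurious risk difference: p × (s1 − s0).
- Spurious risk ratio: s1 / s0, whatever the value of p.
- Chance of a significant result: normal approximation for two proportions, two-sided 5% level, counting rejection in the direction of the distortion.

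| p | s1 v s0 | Recorded | Difference | Ratio | Chance of p < 0.05 |
|---|---|---|---|---|---|
| 10% | 95% v 85% | 9.5% v 8.5% | 1 point | 1.12 | 4.8% |
| 10% | 90% v 70% | 9% v 7% | 2 points | 1.29 | 9.1% |
| 20% | 95% v 85% | 19% v 17% | 2 points | 1.12 | 6.4% |
| 20% | 90% v 70% | 18% v 14% | 4 points | 1.29 | 15.0% |
| 40% | 95% v 85% | 38% v 34% | 4 points | 1.12 | 10.5% |
| 40% | 90% v 70% | 36% v 28% | 8 points | 1.29 | 30.6% |

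Without distortion, the chance of rejection in one given direction is 2.5%. Either arm could be the one with fuller detection, so the table says nothing about direction.

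**The case against.** The best reply is that the blinding sentence is loosely worded, not false. The secondary aim uses clinical for pain, function, quality of life and global change, set beside MRI outcomes. Adverse events are only additional measures, and the nurse's part is openly disclosed. This has force, and it makes the remedy small. It does not remove the conflict, because the sentence says all and Table 1 places adverse events among the assessments.

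Second, the informant is a blinded participant, and self-report at 2 and 12 months does not pass through the nurse. This stands. It limits the exposure to the injection period and reduces the risk without removing it.

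Third, the adverse-effects section lists what is to be asked (nature, duration, action taken). That can be read as covering both routes, and scripts and forms commonly sit in the full protocol. This is fair: the article does not show that the questioning is unstructured. A script would still not blind the person using it.

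Fourth, different people might share the nurse title. If so, the article needs to say so.

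A reader might go further and infer three things that the article does not support:

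- **That the safety comparison is biased.** No differential elicitation is shown, only an opening for it.
- **That the nurse's conversation cues participants about their group before they are asked to guess it.** Nothing describes the nurse revealing anything, and the order of the two questions after injection 3 is not stated.
- **That short-term reactions are the chief safety difference between PRP and saline.** The article does not say this, and the point does not need it.

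**Conclusion.** The point holds as a conflict within the article and an avoidable weakness in safety ascertainment. The role that knows the allocation elicits adverse events around the injections, against an unqualified statement that clinical assessments are blinded. The injection-period safety comparison is therefore open to ascertainment bias of unknown size and direction. The illustrated range (1 to 8 percentage points, risk ratio 1.12 to 1.29) rests wholly on assumed rates and detection probabilities and is not an estimate for this trial.

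It would be wrong to carry the point over to efficacy. Pain is reported on questionnaires completed at home, and cartilage volume is read from MRI blinded to allocation and time sequence. Neither primary outcome passes through the nurse's question, and no figure in the sample size section changes. The conclusion assumes that the study nurse is one role throughout, as the wording indicates.

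**What to change.** In the Interventions section and the section on adverse effects, replace the nurse's question with a short standard written adverse-event form. The participant completes it at injection visits 2 and 3 before any contact with the study nurse, and receives the same form about 1 week after injection 3. Existing blinded staff code the answers. The injecting doctor should not review the forms before recording a guess of the participant's group: if reactions did differ by arm, the forms could give that doctor clues and damage a blinding claim that the trial intends to test. Add the new time points to Table 1 so that table and text agree.

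If elicitation by the nurse is kept, state the exception beside the blinding statement and report nurse-elicited and self-reported events separately.

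The cost is one form, small edits to the procedure wording and about a minute of participant time per form. No extra staff or visit is needed.
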